**Ethics and dissemination:**

Ethical approval has been obtained. Results will be presented in journal articles, conferences and through varied forms of media to reach policymakers, stakeholders and the public.

Strengths and limitations of this studyThis study uses an iterative staggered design in order to refine an intervention throughout the research process.Measures of acceptability and feasibility of the intervention and of the ability to evaluate it in a rigorous trial setting will be reviewed against continuation criteria throughout the study.Multiple informants will provide relevant data, including school staff and parents, and data on both positive and adverse outcomes will be captured.However, the iterative nature of the study means that different participants will not receive the same intervention, therefore group-level effects cannot be delineated.Alternate analyses will be used to ascertain whether there are patterns of change in symptoms and functioning that replicate across individuals instead.

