## Methods and analysis

### Design

A randomised iterative mixed-methods case-series design will be used. Schools will be the units of randomisation, and will be randomised to the time (school term) when they will use the toolkit. The toolkit will be refined after each school has used it for one term, or more frequently if major issues are highlighted during a school’s use of the toolkit. Small, theory-based and data-driven changes hypothesised to be relevant across the school context will be made, as well as reactive changes addressing barriers to implementation. Randomisation to using the toolkit in different school terms allows for inferences to be made as to whether the intervention is improving outcomes, with consistent improvement following the introduction of the core components enabling researchers to potentially rule out alternative explanations for behaviour change, such as improvement due to other support in place or differences in behaviour across the school year. If baseline symptoms and functioning remain on stable trajectories for children across schools, changing only when the intervention is introduced, this implies it is the intervention rather than an alternate factor stimulating the change. It is a commonly used design for single-subject analyses where the intervention cannot be withdrawn and re-implemented such as in an ABAB design.^25–27^

Eight schools will participate in total in two recruitment cohorts of four (in order to avoid later participating schools having to sign up to the study years in advance); each cohort will enter the study at a different time. Schools in each cohort will then be randomly assigned their individual baseline term in the study using a computerised random sequence generator (see figure 1). The length of the baseline period will be the same for each school (one school term), with schools within each cohort entering their baseline period in different school terms; the term in which the intervention is delivered is therefore staggered across the study (figure 1). This design will allow for refining and adapting the toolkit and its implementation based on ongoing participant feedback, maximising the chances it has of being acceptable and feasible (and therefore suitable for further evaluation in a pilot and then definitive cluster randomised controlled trial) by the end of the study.

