##### Subaim C

Assess whether measures of behaviour, classroom functioning and teacher-reported ADHD symptoms indicate improvement following use of the toolkit. *To explore whether there is indication that the toolkit may be efficacious*, quantitative data will be visually analysed within schools and participants, describing the nature of change over time and in relation to the intervention, following recommendations.^31^ Non-parametric analysis of the data will be considered, for example, by calculating Tau-U statistics. As the toolkit will be refined between schools participating, it would be irrelevant to compare measures across individuals who received different iterations of the toolkit; the focus will therefore be on assessing whether there is initial indication of improvement in outcomes, and whether any effect is replicated across individuals. Comparisons between the magnitude of change seen between those who receive earlier and later iterations of the toolkit will be carried out as it is anticipated that later iterations, modified to be more acceptable and feasible, would result in greater evidence of behaviour change. This will be an exploratory analysis. The core and target behaviours chosen across study participants will also be explored in a descriptive manner in order to assess the use of the behaviour web, targets and modules.

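### Subaim C calls comparison across toolkit iterations irrelevant, then plans an exploratory early-versus-late comparison that cannot separate refinement from calendar time

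*Protocol article*

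**What the plan says.** Subaim C asks whether behaviour, classroom functioning and teacher-rated symptoms improve after the toolkit is used. It relies mainly on visual analysis within schools and participants, and on whether any effect replicates across individuals. On comparing children who had different versions it makes three statements:

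- Such a comparison is set aside: "it would be irrelevant to compare measures across individuals who received different iterations of the toolkit".
- The next sentence commits to one: "Comparisons between the magnitude of change seen between those who receive earlier and later iterations of the toolkit will be carried out". The rationale is that later iterations, having been made more acceptable and feasible, "would result in greater evidence of behaviour change".
- It is qualified: "This will be an exploratory analysis".

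The strengths and limitations list after the abstract takes the first position, saying that "different participants will not receive the same intervention, therefore group-level effects cannot be delineated".

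The Design section gives the structure: "Eight schools will participate in total in two recruitment cohorts of four", and "each cohort will enter the study at a different time". Randomisation comes after that: "Schools in each cohort will then be randomly assigned their individual baseline term in the study using a computerised random sequence generator". The toolkit is refined after each school's term of use, or sooner if major problems appear. The Introduction states that there is no control or comparison group. Subaim A allows a measure found unsuitable to be replaced between iterations, or its collection frequency to change.

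**The concern.** A reader of Subaim C cannot tell whether a comparison across iterations belongs to the plan. One sentence excludes it and the next schedules it, with an expected direction.

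If it is carried out, more change in later schools would match the stated expectation. It would also match anything else that differs between early and late schools: the date, the cohort through which a school was recruited, the research team's growing familiarity with delivery, or a changed instrument. Nothing in Subaim C tells the reader to hold back from the preferred explanation. At stake is whether a drift over time, or a difference between cohorts, gets reported as a sign that refining the toolkit increased its benefit and is then carried into planning of the definitive trial.

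**Working it through.** The plan gives no figure for this comparison, so there is none to reproduce. The check is one of text and design, with a small calculation on cohort overlap.

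**1. Do the two sentences conflict?** The first concerns measures, the second the magnitude of change. They could be reconciled if raw scores were ruled out and within-child change allowed. But the reason given for irrelevance is that the toolkit is refined between schools, so children receive different iterations. A change score from one version and a change score from another differ in exactly that respect. The text draws no distinction between the two kinds of quantity, so the conflict stands.

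**2. Can version be separated from time?** Suppose the version moves on one step per term. Let β be the gain in change score per version step and γ any drift per calendar term. For a school delivering in term t:

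expected change = constant + βt + γt = constant + (β + γ)t

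Only the sum β + γ can be estimated. Refining at other intervals does not help, because the version still only moves forward with time and the article describes no earlier version kept in use beside a later one. There is also no untreated group from which to estimate γ. Randomising schools to terms decides which school gets which term; it does not break the link between term and version. The Design section's argument from staggering concerns whether change begins when the toolkit is introduced in each school. It does not extend to comparing the size of change between versions.

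**3. How far does version overlap with cohort?** Inputs: two cohorts of four schools (Design); three terms per school, for baseline, intervention and follow-up (Table 3); study dates September 2022 to January 2025 (Procedure). Assuming three terms per school year, that period holds about 7 terms, so the latest start is term 7 − 2 = 5.

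Figure 1 is not available, so the layouts below are assumptions. For each, R² = between-cohort sum of squares ÷ total sum of squares of the start terms.

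| Assumed start terms (cohort 1 / cohort 2) | Between | Total | R² |
|---|---|---|---|
| 1,2,3,4 / 2,3,4,5 | 8 × 0.5² = 2 | 12 | 0.17 |
| 1,2,3,4 / 5,6,7,8 | 8 × 2² = 32 | 42 | 0.76 |
| 1,1,2,2 / 3,3,4,4 | 8 × 1² = 8 | 10 | 0.80 |
| 1,1,2,2 / 4,4,5,5 | 8 × 1.5² = 18 | 20 | 0.90 |

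The second layout does not fit the dates: a start in term 8 would end in term 10. The last two have schools of one cohort sharing a term, whereas Design has schools within a cohort starting in different terms. The first layout respects both, and there cohort explains about 17% of toolkit order.

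**4. Is the yardstick constant?** Not necessarily. If a measure is replaced under Subaim A, early and late schools are scored on different scales and their change scores are not directly comparable.

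**The case against.** The strongest reply is that the comparison is openly subsidiary. It is labelled exploratory. Subaim C puts its focus on improvement and on replication across individuals. The Introduction disclaims any aim of assessing effectiveness, and the Sample size section says the study is not powered for a conventional between-individuals analysis. Aims 1 and 2 are judged against Table 2, which contains no early-versus-late criterion, so no progression decision turns on this result. Replacing a measure is only a contingency. The summary statistic and the definition of early and late may properly sit in a fuller document.

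All of this stands, and it limits how serious the point is. It does not settle which of the two sentences applies, and the exploratory label does not tell the reader that version and time are the same axis.

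Three stronger readings are tempting, and the documents do not support them:

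- *That early versus late is simply cohort 1 versus cohort 2.* No split point is given. If each school in a cohort has its own term, the study dates force the cohorts to overlap, and a midpoint split could not then coincide with cohort. It could coincide if schools shared terms, but that is not what Design describes.
- *That children from one school will be counted as independent evidence.* The article names no unit, test or pooled model for this comparison.
- *That the cohorts sit in different seasons.* Four consecutive terms cover all three seasons of a school year, so a seasonal contrast between cohorts is not established.

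**Conclusion.** The point holds as a contradiction within Subaim C, together with a comparison that cannot carry the interpretation anticipated for it.

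The confounding of version with calendar time is complete and does not depend on the layout. It follows from refinement over time without a concurrent control. The mixing with cohort is partial and uncertain: about 17% of toolkit order under the layout that best fits the text, and up to 90% under shared-term layouts. That range rests on assumed layouts and on three terms per school year; Figure 1 would settle it. That cohort entry is not randomised is inferred from the absence of any such description.

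The consequence is confined to one exploratory secondary analysis. It does not touch the feasibility and acceptability aims, but it does affect what the study may say about whether refinement worked, so the text should be corrected.

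**What to change.** Reconcile the two sentences in Subaim C in one of two ways.

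1. **Delete** the early-versus-late comparison and leave the statement of irrelevance as it is.
2. **Keep it as exploratory description only**, and reword the statement of irrelevance to match. Specify one summary of within-child change per school, displayed in randomised order within each cohort and limited to schools measured on the same instrument. Add that toolkit version cannot be separated from calendar time, and that a later-is-better pattern will not be read as evidence that refinement worked.

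No formal test is needed. A randomisation test on the order of schools would guard against chance differences between schools but would leave version tied to term.

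The cost is about two sentences and no new data. The drawback is that, if kept, the early/late result becomes visibly weak evidence.

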#### Missing, unused and spurious data, and inclusion in analysis

All data will be used in analysis. Patterns of missing quantitative data will be evaluated as part of assessing the feasibility and acceptability of the intervention. Missing data could relate to the feasibility and acceptability of the intervention, or the utility and acceptability of the measure itself (i.e., Aim 1 and Subaim A), and so through the qualitative data collection we will aim to elicit how patterns of missing data relate to our aims and make modifications accordingly.

## Ethics and dissemination

### Ethics and governance approval

Ethical approval has been awarded by the University of Exeter College of Medicine and Health Research Ethics Committee (Ref Jan22/B/300). Informed consent will be sought from all adult participants (and by parents for child participants; an example information sheet and consent form are provided in the online supplemental material). Children will provide assent and ongoing assent will be judged by the research team throughout. Should it become clear that a child does not want to continue to participate in data collection or the study, withdrawal will be discussed with parents and school staff. Should a child express that they wish to stop during a single instance of data collection, this will be stopped for that day. The child’s feelings will be respected and discussed with the child, their parents and school staff about their future involvement. Ultimately, decisions will be made in line with the best interests of the child. All data collected will comply with General Data Protection Regulations, being stored on secure servers and only accessible by the research team. Some data will be shared as part of the intervention, for example, teachers’ ratings of ADHD symptoms will be viewable by the SENCo and express permission will be sought for any planned data sharing between participants. Participants will be asked whether their data can be made available following the study for future analysis or related research. Those that consent will contribute their data to a fully anonymised data set accessible to bona fide researchers. There are several operational issues and associated risks that are involved in performing this study. It is possible that the intervention will lead to adverse outcomes^32^ such as study children feeling singled-out from their peers due to the intervention. The planning group will discuss anticipated potential adverse outcomes due to the intervention, and qualitative feedback will be sought from participants both during their use of the intervention and in the follow-up period. Further risks (aside from those detailed in progression criteria in table 2) have been identified and mitigation plans detailed, as well as key study limitations noted (see online supplemental material).

### Dissemination

Participants who consent to their anonymised data being shared for future research purposes will have their data archived in an open access data set. The results from the study will be presented at relevant national and international conferences (eg, the ADHD World Congress, Eunethydis, the Association for Child and Mental Health national conferences). Separate publications will describe: the iterative development process, the main outcomes of the case-series study, development of the resource use tool, and an in-depth qualitative analysis of data collected during the iteration and process evaluation; authorship will be determined using the International Committee of Medical Journal Editors (ICJME) criteria. A detailed dissemination plan and documents will be developed with the planning group and will include blogs and podcasts, recorded and live talks, and events and engagement activities to reach a broader audience of interested stakeholders and policymakers.
